## Abstract

Background: The efficacy of interlimb-coordinated training on gait and upper limb functional improvement remains unclear. The latest published randomized controlled trials have supported the potential benefits of interlimb-coordinated training to enhance gait function. Upper limb functional recovery may also benefit from interlimb-coordinated training since most everyday activities require the coordinated use of both hands to complete a task. This study investigates the efficacy of interlimb-coordinated training on gait and upper limb functional recovery over a short-medium term period. Methods: A total of 226 acute stroke patients will be recruited from four centres over four years. Patients will be randomly allocated to either conventional therapy or conventional therapy plus interlimb-coordinated training. Outcomes will be recorded at baseline, after 2 weeks of intervention, and at 3- and 6-months post-intervention. Gait speed is the primary outcome measure. Secondary outcome measures include Fugl–Meyer Assessment of Motor Recovery, Berg Balance Scale, Timed Up and Go test, Action Research Arm Test, electroencephalography, and magnetic resonance imaging. Conclusion: The results of this trial will provide an in-depth understanding of the efficacy of early interlimb-coordinated intervention on gait and upper functional rehabilitation and how it may relate to the neural plasticity process.

## 1. Introduction

Stroke is among the top-ranked cause of disability-adjusted life years worldwide [1]. It is the leading cause of disability in China [2], with approximately 3 million new stroke cases every year [3], making China the country with the highest prevalence of stroke in the world [4]. The Global Burden of Disease Study [5] stated that more effective interventions are needed. Gait and upper limb dysfunction are common among patients with stroke. Early literature indicated that almost two-thirds of the stroke survivors initially have mobility deficit and that over 30% of stroke survivors could not walk independently [6]. One year after stroke occurrence, half of the stroke survivors could not complete a 6 min walk test, and those who could were only able to achieve 40% of the predicted normal distance [7]. Only 5% to 20% of stroke survivors recovered their upper limb function completely, 25% of stroke survivors recovered part of upper limb function, and 60% of them lost upper limb function completely [8].

Effective gait recovery is essential to safely conduct daily living activities and to improve quality of life [9]. Gait speed is regarded as an indicator for quality of life and further stroke incidence [10]. The average gait speed of healthy individuals in the age group of 40–80 is between 1.26–1.41 m/s for men and 1.13–1.39 m/s [11] for women. Patients with subacute and chronic stroke were reported to have an average gait speed of 0.33 m/s [12] and 0.65 m/s [13] respectively. Despite advancements in rehabilitation technology, 90% of stroke survivors continue to experience mobility impairment [14]. Traditional gait intervention was conducted on the ground or on a treadmill with or without body weight support [15] in order to provide high-intensity, repetitive, task-specific training interventions to promote an improvement in gait function [16]. It has been reported that traditional gait intervention can achieve gait speed improvements of between 0.03 m/s [17] to 0.1 m/s [18]. The average minimal clinically important difference (MCID) for gait speed across patients with different stroke onsets was reported to be 0.175 m/s as the numerical parameter for a meaningful improvement in walking ability [19]. There is emerging evidence to suggest that gait recovery may remain suboptimal due to the fact that the paretic motor neuron pools are only partially activated by the nervous system, and the current gait rehabilitation regime may not be at a high enough intensity to activate these motor neuron pools [20]. Thus, this casts some doubts over the efficacy of traditional walking training in patients who have experienced stroke, and a new rehabilitation strategy is urgently needed. An increasing amount of evidence provides insight into the role of the upper limb, which may potentially play in gait recovery. A study on the effectiveness of stationary cycling training in chronic stroke patients demonstrated a significant improvement in gait [21]. It was suggested that the cycling motion shares a common locomotion pattern with walking based on the reciprocal lower limb muscles coordination [22]. The coordination of four-limb motion has been coined “interlimb coordination”, where all four limbs move in coordination to accomplish a task, and this has been recently proposed to enhance limb movement control through an increase of neural coupling between arms and legs [23]. Examples of interlimb-coordinated tasks are the use of a rowing machine, elliptical machine, and bicycle ergometer [24]. A recently published study that included healthy participants reported that upper limb muscles drive lower-limb muscle activity during a specific gait phase via the subcortical and cortical pathways to achieve intermuscular coherence between the upper and lower limbs [25]. This provides further evidence to support the role of upper limb in gait function and highlights the importance of upper and lower limb coordination to facilitate gait recovery. Rhythmic arm cycling training in patients with chronic stroke was reported to promote a significant improvement in gait, balance, lower limb motor function, and enhanced activity in the dorsiflexion muscle during the swing phase of walking [26]. The most recently published preliminary randomized controlled trial investigated the effect of the interlimb coordinated protocol in patients with chronic stroke [24]. A range of interlimb coordinated tasks were provided to chronic stroke patients for 2 months (3 h per week) in an outpatient setting. The results showed that the interlimb-coordinated training group had significantly higher improvement in their Fugl–Meyer Assessment scores, Rivermead Visual Gait Assessment, and modified Rankin Scale than the control group, providing some support for the potential role of the upper limbs in gait function recovery and the potential benefits of interlimb-coordinated intervention [27]. However, the study that adopted interlimb-coordinated intervention was a preliminary trial without adequately powered sample calculation, increasing the likelihood of a type II error. In addition, patients with chronic stroke were recruited in the study, and it remains unclear as to whether interlimb-coordinated intervention could be adopted during the acute phase. The neural plasticity changes induced by interlimb-coordinated intervention are unknown as no studies have investigated the changes at a cortical level. However, studies conducted in healthy individuals showed stronger activations of the cortex supplementary motor area (SMA), premotor area [28], and cerebellum [29] during ipsilateral arm and leg movement in the opposite direction than during ipsilateral arm and leg movement in the same directions and during single-limb movement. Thus, it is logical to expect that stroke patients who have undergone interlimb coordinated intervention may have stronger cortical activation that correlates with an improvement in gait function. To date, only one study has been found that investigated the neural integrity at the spinal level induced by arm cycling [26], which confirmed its modulation effect on gait and balance in chronic stroke patients. The neuroplasticity at the cortical level induced by interlimb-coordinated intervention remains unclear. It is also unknown if interlimb-coordinated intervention may yield that is in comparable clinical benefits to those observed in the chronic stroke phases when provided at the acute stages.

Upper limb functional recovery in order to perform fine motions, such as grasping, finger pinching, and individual finger dexterity, continues to be a challenge for stroke survivors [30]. The majority of everyday activities require the coordinated use of both hands [31]. It is common that one of the upper limb stabilizes a trunk or an object itself in order to allow manipulation by the other limb, or both of the upper limbs may be needed to manipulate the object for a task to be completed [24]. The impairment of bimanual coordination in patients with stroke have been reported in several studies, and impairments in coordination are not related to the lateral deviation of the impaired limb [32,33]. A large scale systematic review attempted to identify which type of intervention promotes arm and hand functional recovery post stroke, and the authors reported that no high-quality evidence was available to support any of the interventions that are currently used as part of routine practice [34]. The majority of the published literature investigated the efficiency of single-limb rehabilitation regimes, such as a single-armed robotic device [35], constraint-induced movement therapy [36], or commercial gaming devices such as the Microsoft Xbox [37]. While these intervention regimes demonstrated various degrees of success in upper limb functional recovery and cortical reorganization, the general results of upper limb function recovery remain unsatisfactory, as evidenced by the fact that a large proportion of patients with stroke continues to have an upper limb functional deficit years after stroke occurrence. Thus, patients with stroke may theoretically benefit more from bimanual training tasks than unimanual tasks. A preliminary study that compared the benefits between single-limb training with double-limb robotic devices reported results favouring double-limb training [27]. To date, there is also insufficient evidence to demonstrate whether interlimb-coordinated intervention is beneficial in upper limb function recovery when it is provided at the acute stage. 

The primary aim of the present study is to investigate the effect of interlimb-coordinated intervention on gait and motor function in patients with stroke at the acute stage. It is hypothesized that acute stroke patients who receive interlimb-coordinated intervention will significantly improve gait and upper-limb motor function. These improvements would be significantly higher than those who receive conventional therapy immediately after the 2 weeks of intervention and at the 3- and 6-month follow-up periods. The secondary aim is to investigate the neural plasticity changes that are induced by interlimb coordinated intervention after 2 weeks of intervention and at the 3- and 6-month follow-up periods. It is also hypothesized that the participants who undergo interlimb-coordinated intervention would have stronger cortical activation at rest and during gait and a shorter neural processing time to initiate a motor task than the participants in the control group immediately after intervention and at the 3- and 6-month follow-up periods. 

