### 2.7. Outcome Measures

#### 2.7.1. Primary Outcome Measure

The primary outcome measure is gait speed, which will be assessed by the 10 m walk test. 

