### 4.2. Data Analysis

All statistical analyses will be performed in IBM SPSS version 21 software (SPSS Inc., Chicago, IL, USA). Descriptive statistics will be conducted to describe the sample population. The demographic characteristics and baseline results for the primary and secondary outcome measures will be analyzed using analysis of variance (ANOVA) or Chi-square test for categorical data. A mixed-effect model analysis will be adopted to compare changes in all of the outcome measures between groups at the completion of the intervention and at the 3- and 6-month follow-ups. The mixed-effect model analysis will include treatment, time, and centre as fixed effects, and the participants will be included as the random effect. Changes in the outcome measures will be adjusted for age, sex, centre, and time. The level of statistical significance will be set at *p* < 0.05. Cohen’s d will be calculated to measure the effect size of the difference for every comparison. The effect size will be interpreted as follows: 0.2—small effect size; 0.5—medium effect size; and 0.8—large effect size. Stratification analysis will be conducted to explore the potential effect difference between centres. There are no planned interim analyses or stopping rules, as the power calculation has accounted for loss to follow-up. In the event of missing data during the follow-up period, the modified intention to treat principle will be followed with the last observation carried forward method. 

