## 6. Conclusions

The results of this trial will provide an in-depth understanding of the efficacy of early interlimb-coordinated intervention on gait and upper functional rehabilitation and how it may relate to the neural plasticity process.

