**Figure 3 brainsci-11-01495-f003:**
[figure not shown]
Bicycle ergometer for interlimb coordinated intervention.

**Table 1 brainsci-11-01495-t001:** A brief description of each of the secondary outcome measure that will be recorded at all participating centres.

Fugl-Meyer Assessment of Motor Recovery (FMA) [46]	It is a validated tool to evaluate motor function, balance, and joint function in stroke-related hemiplegic patients. The interpretation of FMA is as follows: <50 = Severe; 50–84 = Marked, 85–94 = Moderate; 95–99 = Slight.
Berg Balance scale (BBS) [47]	The BBS consists of 14 balance-related tasks that include sit to stand, stand to sit, and standing on one foot. It was developed to assess the ability to maintain dynamic and static balance.
Timed up and go test (TUG)	The test requires the person to rise from a chair and walk 3 m at a comfortable pace, turn around at the 3 m mark, and walk back to the starting point. The test’s score is the time it takes the person to complete the test. A cut off of 14 s was proposed to be “normal” [48].
Action Research Arm Test (ARAT) [49]	ARAT is a 19-item test that is divided into four sub-tests, which consist of grasp, grip, pinch, and gross arm movement. A score of between 0 to 4 is given to each task: 0—can perform none of the test; 1—performs part of the test; 2—takes abnormally long or has great difficulty in completing the test; 3—able to perform the test normally.
Instrumental Activities of Daily Living (IADL) [50]	The IADL [26] is a functional disability scale that assesses the functional level by asking whether a person receives personal help with daily living activities, such as using the telephone, getting to places outside the house, grocery shopping, preparing meals, doing housework or handyman work, laundry, taking medications, and managing finances.
Electroencephalography (EEG)/Event related potential (ERP)	Parameters of contingent negative variation (CNV), alpha, beta, gamma, and theta wave oscillation.
Functional magnetic resonance imaging (fMRI)	The voxel count T1-weighted data set of the entire brain will be acquired for each participant. The scan parameters for blood oxygen level-dependent weighted scans are as follows: TR = 200 ms, TE = 25 ms, field of view 200 × 200, matrix 64 × 64, and a slice thickness of 3 mm.

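### The primary hypothesis covers gait and upper-limb motor function, but only gait speed is a primary outcome; the upper-limb half has no deciding endpoint and no link to the gait result

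*Protocol article*

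**What the plan says.** All references are to the protocol article.

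- **Introduction, aims.** "The primary aim of the present study is to investigate the effect of interlimb-coordinated intervention on gait and motor function". The hypothesis that follows names both domains: "It is hypothesized that acute stroke patients who receive interlimb-coordinated intervention will significantly improve gait and upper-limb motor function". It expects superiority over conventional therapy "immediately after the 2 weeks of intervention and at the 3- and 6-month follow-up periods". The secondary aim concerns neural plasticity only, so the aims do not place upper-limb function in the secondary tier.
- **Section 2.7.1.** "The primary outcome measure is gait speed, which will be assessed by the 10 m walk test". No upper-limb measure is primary.
- **Section 2.12.** The sample size is built on gait speed alone.
- **Abstract, Section 2.7.2 and Table 1.** The upper-limb measures are secondary. On the first scale, Table 1 says: "ARAT is a 19-item test that is divided into four sub-tests". The second is the Fugl-Meyer. Table 1 describes it as covering motor function, balance and joint function, while Table 2 lists FMA-UL.
- **Section 4.2.** "A mixed-effect model analysis will be adopted to compare changes in all of the outcome measures between groups", at the end of intervention and at 3 and 6 months. "The level of statistical significance will be set at *p* < 0.05". The section gives no order of testing, no adjustment and no condition linking the upper-limb tests to the gait test.
- **Section 6.** The expected yield is an understanding of the "efficacy of early interlimb-coordinated intervention on gait and upper functional rehabilitation".

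**The concern.** The aims put two domains into the primary hypothesis, and the methods support only one. The upper-limb half has no primary endpoint, no sample-size basis and no stated significance level of its own. The plan names no deciding scale if ARAT and Fugl-Meyer disagree and no deciding visit if the effect appears at one time but not another. Because Tables 1 and 2 differ, it is not even settled whether the second scale is an upper-limb measure.

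What is at stake is what the trial may claim. If gait speed shows nothing and one upper-limb comparison reaches p < 0.05, nothing written stops that result from being presented as support for part of the primary hypothesis. Choosing a single visit for gait speed would not settle this, since the upper-limb claim would remain just as open.

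**Working it through.** **1. What the sample size covers.** Inputs from Section 2.12: means 0.69 and 0.39, SD 0.75, power 95%, effect size 0.2. Assumed, because not stated: 4 visits (m) and between-visit correlation ρ = 0.5.

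- f = 0.3 / (2 × 0.75) = 0.20.
- For repeated-measures ANOVA, between factors: λ = f²·N·m / (1 + (m − 1)ρ) = 0.04 × 206 × 4 / 2.5 = 13.18. With 1 and 204 degrees of freedom and alpha 0.05, power is 0.951.
- The stated 206 is therefore reproduced. 206 × 1.10 = 226.6, which the plan takes as 226.

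Every input is for gait speed. No upper-limb quantity enters.

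**2. Number of upper-limb tests.** Section 4.2 compares each outcome at three times, so two scales give 2 × 3 = 6 tests. This counts the Fugl-Meyer as an upper-limb scale, as in Table 2. Read literally, however, the model has treatment, time and centre as fixed effects and no treatment-by-time term. That gives one treatment test per scale, so 2 tests.

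**3. Chance of at least one p < 0.05 when there is no effect.** This applies an any-one-counts rule, which the protocol does not state. Two-sided tests are assumed, since sidedness is not given.

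Independent tests:
- Six, either direction: 1 − 0.95⁶ = 26.5%.
- Six, favouring the intervention: 1 − 0.975⁶ = 14.1%.
- Two, either direction: 1 − 0.95² = 9.75%.

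Correlated tests were simulated as multivariate normal, 400,000 draws per setting. The correlation between two tests is the product of a between-visit and a between-scale value. The document gives neither.

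| Between visits / between scales | Either direction | False benefit only |
|---|---|---|
| 0 / 0 (exact) | 26.5% | 14.1% |
| 0.5 / 0.5 | 21.9% | 11.0% |
| 0.7 / 0.7 | 17.7% | 8.8% |
| 0.8 / 0.8 | 14.9% | 7.4% |
| 0.9 / 0.9 | 11.6% | 5.8% |

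If all six tests are instead equally correlated (1,000,000 draws), the figures are 20.8% and 10.4% at 0.5, and 10.8% and 5.4% at 0.9. The nominal rates for comparison are 5% in either direction and 2.5% for false benefit.

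**4. The opposite rule.** If all six tests had to favour the intervention significantly, the error would be below 1% in every setting simulated (0.63% at 0.9/0.9). The 95% power in step 1, computed for gait speed alone, would then not describe the power for the primary hypothesis.

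**The case against.** The strongest reply is that the methods do rank the outcomes: gait speed is primary, ARAT and Fugl-Meyer are secondary, and the Introduction is only loosely worded. Multiplicity rules for secondary outcomes are commonly left to a statistical analysis plan, which is not shown here. This stands as far as it goes. The absence of a multiplicity rule for secondary outcomes in a condensed article is not itself the fault. The reply does not remove the contradiction in the shown text, where the primary hypothesis includes a domain that the outcome section makes secondary and Section 4.2 applies one threshold to everything.

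A reader might infer more: that the upper-limb claim carries a false-positive risk of about 22%, and that one significant result out of six confirms half of the primary hypothesis. The documents do not support that.

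- The 22% needs correlations of 0.5 that appear nowhere in the protocol.
- It counts results favouring control. For a false claim of benefit, the figure under the same assumption is 11%.
- It needs the any-one-counts rule. The hypothesis joins the domains and the visits with *and*, which points the other way if taken strictly.
- The model as listed may yield only one test per scale.

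Nor does Section 6 set a criterion for success; it describes what the trial is expected to inform.

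**Conclusion.** The point holds as an inconsistency with consequences for the claims. The primary aim and hypothesis cover gait and upper-limb motor function, while the primary outcome and sample size cover gait speed only. For the upper limb, the shown text fixes no deciding scale, no deciding visit and no relation to the gait result.

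The size depends on a decision rule that the protocol leaves open:

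- **Any one of six counts:** about 11% to 26% in either direction (21.9% at 0.5/0.5), and about 6% to 14% for false benefit (11.0% at 0.5/0.5). The low ends are for correlations of 0.9.
- **One test per scale, either counts:** at most about 9.75% in either direction.
- **All six must succeed:** no inflation, but the stated power does not apply to the hypothesis.

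The correlations and two-sided testing are assumptions. The mismatch itself depends on none of them.

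**What to change.** 1. In the Introduction, reword the hypothesis so that gait speed alone carries the primary hypothesis and upper-limb function is secondary.
2. In Section 4.2, name one upper-limb endpoint and one visit, for example ARAT at the same visit as the primary gait contrast. Test it at 0.05 only if gait speed is significant. This fixed order keeps the chance of a false claim across the two tests at 5%, provided the gait test is itself a single contrast.
3. Report the other upper-limb scale and the other visits as supportive estimates with 95% confidence intervals that cannot confirm the primary hypothesis.
4. Reconcile the general Fugl-Meyer in Table 1 with FMA-UL in Table 2.

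This point requires no change to BBS, TUG or IADL. The cost is wording only: no added participants, visits or data, and the planned 226 stands. The downside is that an upper-limb effect without a gait effect could be reported only as exploratory.

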## 2. Materials and Methods 

### 2.1. Study Design

This study is a parallel, single-blinded, multi-center randomized controlled trial to evaluate the effect of interlimb-coordinated intervention on gait and motor function recovery in patients with acute stroke. 

